## Abstract

**Background:**

Shared decision making is a promising model for patient-centred medicine, resulting in better clinical outcomes overall. In the mental health field, interventions that consider the patient-centred perspective—such as patient quality of life, involvement in the treatment, treatment satisfaction, and working alliance—have increased and better clinical outcomes discovered for patients with schizophrenia. However, few studies have examined the efficacy of shared decision making for schizophrenia treatment. The objective of this study is to evaluate the effect of a shared decision making intervention compared to treatment as usual on patient satisfaction at discharge for first-admission patients with schizophrenia.

**Methods/Design:**

This is a randomised, parallel-group, two-arm, open-label, single-centre study currently being conducted in an acute psychiatric ward of Numazu Chuo Hospital, Japan. We are recruiting patients between 16 and 65 years old who are admitted to the ward with a diagnosis of schizophrenia without prior experience of psychiatric admission. Fifty-eight participants are being randomised into a shared decision making intervention group or a treatment as usual control group in a 1:1 ratio. The intervention program was developed based on a shared decision making model and is presented as a weekly course lasting the duration of the patients’ acute psychiatric ward stay. The primary outcome measure is patient satisfaction at discharge as assessed by the Client Satisfaction Questionnaire. Due to the study’s nature, neither the patient nor staff can be blinded.

**Discussion:**

This is the first randomised controlled trial to evaluate the efficacy of shared decision making for patients with early-treatment-stage schizophrenia. The intervention program in this study is innovative in that it includes both of the patient and staff who are involved in the treatment.

**Trial registration:**

The study has been registered with ClinicalTrials.gov as NCT01869660.

## Background

The healthcare systems in developed countries are evolving from a paternalistic to a patient-centred approach in which patients are more informed and take more active roles in decision making [1,2]. Shared decision making (SDM) is a promising model for the movement in which patients and clinicians share all information and individual preferences regarding the treatment through the entire decision making process [3]. A systematic review of 86 randomised trials found that SDM, when compared to usual care, resulted in patients gaining more knowledge, increased confidence in decisions, and more active patient involvement. These results were found across several fields of medicine, such as cancer treatment [4].

In the mental health field, treatment adherence has remained a common issue over several decades, particularly for patients with schizophrenia. A systematic review found that 49.5% of patients with schizophrenia were estimated to be non-adherent to antipsychotic medication [5]. Numerous interventions have attempted to address this issue, including psychoeducation, motivational and behavioural therapy, family therapy, and telephone call prompts. However, randomised controlled trials and reviews of those interventions have not found enough evidence regarding how to increase adherence, particularly in long-term follow-up studies [6-11]. Therefore, interventions that do not only focus on improvement to adherence but also consider the patient-centred perspective—such as the patient’s quality of life, involvement in the treatment, treatment satisfaction, and working alliance—have increased, thereby resulting in better clinical outcomes for patients with schizophrenia [12-14]. Attempts to find appropriate approaches for better clinical outcomes for patients with schizophrenia are being undertaken and SDM is expected to be one of them.

To the best of our knowledge, there are only three randomised controlled trials examining the efficacy of SDM for schizophrenia treatment. Hamann conducted of them [15,16], comparing SDM intervention with usual care for inpatients with schizophrenia. In the first study, patients (n = 107) in the intervention group were given decision aids that contained information about pharmacological and psychoeducational treatment options. Patients in the intervention group did not differ in their results from the patients in the control group who were given treatment as usual (TAU) in terms of overall treatment satisfaction, but it did improve their treatment knowledge. In the second study (n = 61), patients in the intervention group attended a shared decision making training program consisting of five one-hour group sessions. The intervention yielded higher participation preferences and increased patients’ desire to have greater responsibility in treatment decisions than in the TAU program; this continued to the six-month follow-up. Krieke [17] evaluated an Internet-based decision aid for schizophrenia (n = 250) in an outpatient setting. Patients in the intervention group were offered the opportunity to make use of the Internet-based information and decision tool. This tool was designed to support patients in acquiring an overview of their needs and appropriate treatment options as provided by their mental health care organisation. Patients in the control group were given their usual care. No differences were found between the intervention and control groups regarding perceived involvement in medical decision making.

More studies are needed to determine the efficacy of SDM for schizophrenia treatment. To confirm what former studies have not—namely, reducing patients’ heterogeneity and developing an intervention that targets both patients and staff—we are conducting this study of SDM for first-admission patients with schizophrenia.

### Objectives

The objective of this study is to evaluate the effect of an SDM intervention compared to TAU on patient satisfaction at discharge and treatment continuation six months post-discharge for first-admission patients with schizophrenia.

## Methods/Design

### Trial design

This is a randomised, parallel-group, two-arm, open-label, single-centre study currently being conducted in an acute psychiatric ward in Japan. It has been approved by the Yokohama City University Medical Research Ethics Committee and registered at ClinicalTrials.gov (registration number: NCT01869660). To avoid biased allocation, randomisation is undertaken by central allocation using a computerized random number generator at the Internet Data and Information Center for Medical Research (INDICE), provided by the University Hospital Medical Information Network (UMIN) in Japan. After written informed consent has been obtained, randomisation is performed to assign patients, in a 1:1 allocation ratio, to either the SDM model intervention or TAU with stratification by sex, age (under or over 20 years old), and assumed duration of illness (less or more than one year) via the minimisation method. Due to the nature of the study, neither the patient nor staff can be blinded. Figure 1 provides an overview of the trial flow. Additional file 1 depicts a summary of the study parts and their timing in the intervention and control groups. We estimate that data gathering will be completed in March 2015.

**Figure 1 F1:**
[figure not shown]
Flow diagram; it provides an overview of the trial flow from baseline assessment at the admission to the follow-up at 6 months after the discharge.

### Study setting

We are conducting our study in an acute psychiatric ward of Numazu Chuo Hospital, a psychiatric hospital with five wards (286 beds in total) in a suburban area of Shizuoka prefecture, Japan. Serving a catchment area of 830,000 people, it is the only psychiatric hospital in the area that accepts emergency admissions 24 hours a day, 365 days a year. On average, approximately 400 people are admitted to the ward in a year and two-thirds of these people are diagnosed with schizophrenia (ICD-10 codes: F20–F29). Approximately 90% of admissions are legally involuntary. The average duration of hospitalisation in the ward is 45 days.

### Eligibility criteria

Participants will be eligible for inclusion in the study if they meet the following criteria: (1) admittance to the acute ward at Numazu Chuo Hospital, (2) schizophrenia diagnosis (ICD-10 codes: F20–F29), (3) aged 16 to 65 years old at admission, and (4) has no prior experience of psychiatric admission (first admission).

Participants are excluded if they (1) are diagnosed with moderate to severe mental retardation, (2) are diagnosed with any of the organic mental disorders (ICD-10 codes: F00–F09), (3) do not have sufficient Japanese language knowledge, or (4) have severe conceptual disorganisation as measured by the Japanese version of the Brief Psychiatric Rating Scale (BPRS; rating of five or more) [18,19]. The cut-off point was decided by referring to prior studies of SDM for inpatients with schizophrenia by Hamann [15,16].

### Intervention

We developed the SDM model program as an inpatient intervention that focuses on the very basics SDM; that is, how patients and medical staff share information and patients’ own preferences regarding the on-going treatment [3].

The program is a weekly course lasting the duration of the patients’ acute psychiatric ward stay, with a maximum of 90 days. Sessions are held on a certain day and time every week during the hospitalisation. They involve three sequential elements: (1) the patient answers the questionnaire regarding their perception of on-going treatment, (2) the patient and staff hold the session in which they share information and their preferences, and (3) the patient and staff create a weekly care plan sheet.

First, participants are asked to complete a six-item self-reported questionnaire that assesses patients’ perceptions of their treatment at the time. The questionnaire (Additional file 2) is an initial intervention tool allowing patients to express themselves more easily and prepare for the following session. Each question is written in a simple sentence, and is designed to be answered using a five-point Likert scale. In order to avoid perceived pressure from staff, the patient is asked to answer in private setting or with the help of a staff member if the patient requests assistance.

Second, to discuss patients’ and medical teams’ perceptions of treatment, patients in the SDM intervention attend a group session. The members of each session are the patient, medical team (i.e. the primary doctor, the primary nurse, and other staff), and a facilitator from the supervision team. Regarding the questionnaire that the patient has answered, the patient and at least three ward staff members discuss for 15–20 minutes the on-going treatment, including medication, ward circumstances, and treatment goals. A facilitator from the study supervision team presides, trying to create a comfortable atmosphere both for the patient and staff members. Other participants are free to discuss their own views and preferences regarding the treatment.

Third, all the session’s participants draft the care plan sheet in order to outline clearly what they have shared in the session. The sheet displays the treatment information at that point in time, including remaining symptoms, diagnosis, the patient’s condition, medication, problems at the ward and solutions, activities, and the goal of hospital treatment. Additional file 3 indicates an example of the care plan sheet.

To standardise and improve adherence to the study, five staff members who are independent from the patient’s treatment are organized into a project supervision team. This team has four duties. First, the team delivers a brief 20-minute lecture regarding the basic theory of SDM to all of the psychiatrists, nurses, social workers, and pharmacologists who work at the ward, prior to their participation in the intervention. Second, the team manages the intervention schedule and facilitates sessions each week. Third, throughout the study period, the team stays in the ward and occasionally provides feedback to participating staff to establish the integrity of the intervention. Fourth, before the weekly intervention session, the team assesses the patient’s condition. If the patient’s condition deteriorates and does not meet the eligibility criteria—for example, conceptual disorganisation worsens to a greater-than-five ranking as per the BPRS—the team postpones the session until the patient recovers.

### Control group

The control group receives TAU, which is mainly medication treatment. During the hospitalisation period, doctors examine patients daily and nurses care for patients by assisting them in their self-care activities and encouraging them to participate in the unit’s daily activity program. Although the primary doctor and nurses discuss the patient’s overall progress and plan for discharge on a regular basis, there is no fixed occasion for the patient and staff to share all of the information. Moreover, there is no specific chance for the patient to be introduced to the concept of SDM or to actively participate in the treatment.

### Primary outcome

This is the patient’s satisfaction at discharge as assessed by the Japanese version of the Client Satisfaction Questionnaire (CSQ-8J) [20,21], a self-report scale containing eight items clustered into four response categories. The overall score is the sum of the item responses; it ranges from 8–32, with higher scores indicating higher satisfaction. The CSQ-8 has been used frequently in clinical trials of schizophrenia [22-24], such as the randomised controlled trials of SDM for schizophrenia by Hamann [15,16]. The Japanese version has good internal consistency (Cronbach’s α = 0.83) and moderate convergent validity (r = .36–.49) with another self-report instrument for client satisfaction inquiry [24] when used for psychiatric inpatients at discharge [21].

### Secondary outcome

These are attitudes toward medication, symptom severity, and treatment continuation. The Japanese version of the Drug Attitude Inventory-10 (DAI-10) [25,26] is used to measure attitudes toward medication. It is a 10-item self-report instrument, with each item being rated as either true or false with regard to the nature of patient experiences with psychotropic drug use. Scores range from -10 to 10, with higher scores indicating a more positive attitude towards medication. The DAI-10 is administered at discharge in the study. The Japanese version of the BPRS, Oxford version, is used to assess symptom severity, which the ward doctor undertakes routinely for all the patients at admission and discharge. Treatment continuation is assessed from their medical records if the patient continues treatment at the Numazu Chuo Hospital and, if not, by asking patients via a telephone call six months post-discharge.

### Sample size calculation

The primary outcome is the mean difference in treatment satisfaction as measured by the CSQ-8J between the SDM group and the TAU group at the time of discharge from the acute psychiatric ward. In the study by Loh et al. [27], among patients with newly diagnosed depression in primary care settings, the standardised mean difference between a SDM intervention group and a TAU group for the CSQ-8 was 0.92. We expect a smaller effect size of 0.80 because the study population of first-admitted patients with schizophrenia is a potentially more complex problem. Assuming a power of 80% and two-sided significance level of 5%, we estimate that a sample size of 26 patients per arm is required to detect an effect size of 0.80. In order to adjust for loss of power due to an anticipated drop out of 10%, 58 patients will be included.

### Statistical methods

The data will be analysed on an intention-to-treat principle. Multiple imputation methods [28] will be used for imputing any missing information regarding outcome measures. Unadjusted comparisons of outcome measures between the groups (SDM vs. TAU) will be conducted using Student’s t test or Mann-Whitney U test, depending on the variable distribution for continuous variables (i.e. treatment satisfaction, attitude toward medication, and symptom severity) and chi-squared test for the categorical variable (i.e. treatment continuation). To control characteristics such as sex, age, and duration of illness, we will use a general linear model or a generalised linear model with log-link function, depending on the variable distribution for the continuous variables and a logistic regression model for a categorical variable. Analyses will be performed using R version 3.0.2.

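### The primary outcome is defined as a mean difference in CSQ-8J, but the analysis lets the score distribution choose among methods that do not all report one, and names none as primary

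*Protocol article*

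**What the plan says.** Protocol article, Sample size calculation, sets the target in these words: "The primary outcome is the mean difference in treatment satisfaction as measured by the CSQ-8J between the SDM group and the TAU group", measured at discharge. The section then plans on a standardised mean difference: "We expect a smaller effect size of 0.80", and "we estimate that a sample size of 26 patients per arm is required to detect an effect size of 0.80". With dropout it reaches the total: "anticipated drop out of 10%, 58 patients will be included".

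Protocol article, Statistical methods: continuous outcomes, with treatment satisfaction listed first, are compared without adjustment by Student's t "test or Mann-Whitney U test, depending on the variable distribution for continuous variables". The adjusted analysis, which controls for characteristics such as sex, age and duration of illness, is a linear model or a log-link generalised linear model, again according to the distribution. Multiple imputation "will be used for imputing any missing information regarding outcome measures". The section gives no criterion for judging the distribution and does not say whether the unadjusted or the adjusted comparison is the primary one.

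**The concern.** One section fixes the quantity of interest and the next unfixes it. A t test and a linear model both address the difference in means. Mann-Whitney addresses whether scores in one arm tend to exceed those in the other. A log-link model addresses the ratio of means. A reader of the Statistical methods section cannot tell which number will be reported as the primary result.

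The switch could well be used. CSQ-8J is bounded at 8 and 32, so satisfaction scores may pile up towards the ceiling. Patients and staff are not blinded, so a choice of method left open is a choice that could be made, or be suspected of having been made, with knowledge of the results. At stake are a clearly defined primary effect and the credibility of its p-value.

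**Working it through.** **1. The plan's own sample size.** Inputs from Sample size calculation: standardised difference d = 0.80, power 80%, two-sided 5%, dropout 10%.

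- Normal approximation: n = 2(1.960 + 0.842)² / 0.80² = 24.5, so 25 per arm.
- Noncentral t, with 2n − 2 degrees of freedom and noncentrality d√(n/2): power is 79.1% at n = 25 and 80.7% at n = 26, so 26 per arm.
- Dropout: 52 / 0.90 = 57.8, so 58.

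The stated 26 and 58 reproduce exactly, as a t test of means.

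**2. What each permitted method addresses.**

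| Method | Quantity | A mean difference? |
|---|---|---|
| Student's t | difference in means | yes |
| Mann-Whitney | P(X > Y) + ½P(X = Y) against ½ | no |
| Linear model | adjusted difference in means | yes |
| Log-link model | adjusted ratio of means | no; needs a further step that is not described |

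Log-link illustration, with an assumed SD of 4.5: 0.80 × 4.5 = 3.6 points. For assumed control means of 20, 22 and 24, the ratio is 23.6/20 = 1.18, 25.6/22 = 1.16 and 27.6/24 = 1.15. One mean difference corresponds to several ratios.

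**3. Behaviour of the choice.** Simulation with 10,000 runs per scenario and 26 per arm, scores rounded and clipped to 8-32. None of the score distributions is in the documents; all are assumed:

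- near-normal: mean 22, SD 4.5;
- ceiling-skewed: 32 minus a gamma variable of shape 1.8;
- opposite skew: 22 plus or minus a centred gamma variable, both means 22.0, SD 2.1.

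The rule is also assumed: use Mann-Whitney if Shapiro-Wilk gives p < 0.05 in either arm, otherwise t. Monte Carlo standard error near 5% is √(0.05 × 0.95 / 10,000) = 0.2 points. Entries are the percentage of trials with p < 0.05.

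| Scenario | t | Mann-Whitney | Rule | Smaller p |
|---|---|---|---|---|
| Near-normal, no effect | 4.9 | 4.9 | 5.1 | 5.8 |
| Ceiling-skewed, no effect | 4.9 | 4.8 | 5.1 | 6.4 |
| Equal means, opposite skew | 5.6 | 12.4 | 12.5 | 13.4 |
| Near-normal, d = 0.80 | 79.8 | 77.9 | 79.5 | 81.2 |
| Ceiling-skewed, means 24 and 27 | 58.1 | 51.8 | 52.4 | 61.0 |

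- With identical distributions in the two arms, the rule holds about 5%. A separate set of runs gave 4.7-5.2% for the rule and about 6-7% for the smaller p-value.
- The third row shows that Mann-Whitney can reject often when the means are equal. It is a constructed case that demonstrates a different target, not a forecast for this trial.
- In the last row the rule chose Mann-Whitney in 94% of trials and lost about 6 points of power against t (58.1 − 52.4 = 5.7). The two tests disagreed on significance in 12% of trials. A separate run under ceiling skew gave 44% for the rule against 50% for t.

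**The case against.** The strongest reply is that the written rule depends on the distribution, not on the p-value, and that such a rule keeps type I error near 5%. That stands. A reader might infer that the plan as written carries a 6-7% false-positive rate; it does not. That figure describes picking the smaller p-value, which nothing in the article proposes.

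Four other tempting readings also go too far.

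- **Choice after unblinded data.** The article does not say when the distribution is judged, or by whom. A pooled, allocation-blind check is compatible with the text.
- **Four routes to significance.** Distribution selects one method within each pair. Having both an unadjusted and an adjusted comparison is a separate matter, namely that neither is named as primary. It would remain with t and the linear model alone, where taking the smaller p-value rejected in 5.6-6.1% of null trials in one run.
- **Log link tests a different hypothesis.** In the unadjusted two-group case, a ratio of 1 and a difference of 0 are the same null. What changes is the scale of the reported effect.
- **Mann-Whitney is incompatible with the imputation plan.** A U statistic does not fit directly into Rubin's rules. But the article does not say how results are combined across imputations, and that detail can belong to the full plan.

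It may also be said that an unseen analysis plan could settle the choice. It could, but it would have to override the article, which positively states a distribution-dependent choice for its primary outcome.

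**Conclusion.** The point holds in a limited form. Sample size calculation names a mean difference. Statistical methods allows methods that test something else (Mann-Whitney) or report on another scale (log link), and designates none as primary. The harm is an effect measure that is not fixed, with room for selective choice in an open-label trial.

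In size this is modest. Type I error is about 5% if the choice is mechanical, and about 6-7% only as a worst case. Under one assumed ceiling-skewed shape, following the rule cost about 6 points of power. These figures rest on assumed score distributions and an assumed Shapiro-Wilk trigger. The mismatch between the two sections rests on the text alone. The sample size is not in question.

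**What to change.** In Statistical methods, remove the distribution-dependent choice for CSQ-8J and name one primary analysis in advance: the linear model adjusted for the minimisation factors (sex, age under or over 20, duration of illness under or over one year). Report the adjusted mean difference with a 95% CI, and pool estimates and standard errors over imputations by Rubin's rules. Keep the unadjusted t test, Mann-Whitney and the log-link model as labelled sensitivity analyses.

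The cost is wording only; 26 per arm and 58 in total are unchanged. The one downside is that a rank test could have slightly more power for some skewed score shapes, although it had less in the ceiling-skewed case checked here.

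### The symptom-severity analysis does not name the admission BPRS as a covariate, although every patient has one, and does not say whether the outcome is the discharge score or the change

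*Protocol article*

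**What the plan says.** Under Secondary outcome, the Protocol article makes BPRS the measure of symptom severity, "which the ward doctor undertakes routinely for all the patients at admission and discharge". A baseline value of this outcome is therefore planned for everyone.

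Under Statistical methods, the unadjusted comparison by Student's t test or Mann-Whitney U test covers the "continuous variables (i.e. treatment satisfaction, attitude toward medication, and symptom severity". The adjusted analysis is then introduced: "To control characteristics such as sex, age, and duration of illness, we will use a general linear model", with a log-link generalised linear model as the alternative where the distribution calls for it. The article does not say which of the two analyses is the main one.

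The three characteristics named are also the minimisation factors under Trial design: "with stratification by sex, age (under or over 20 years old), and assumed duration of illness (less or more than one year". BPRS is not among them.

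The article does not state whether the symptom-severity variable is the discharge score or the change from admission.

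**The concern.** The score of a scale at entry is usually an obvious candidate to predict its later score. Here it will be on file for every patient, yet the stated analysis commits to no use of it. A two-sample test on discharge scores cannot use it, the adjusted model does not name it, and minimisation does not balance it.

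Two things are at stake in a trial of this size. The first is precision: variation in discharge BPRS that admission BPRS explains stays in the error term. The second is chance imbalance: if one arm happens to be more severely ill at entry, part of that difference reappears in the discharge comparison and cannot be told apart from an effect of the intervention.

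Leaving the outcome variable open adds to this. Discharge score, change score and covariate-adjusted discharge score can give different answers from the same data, and the trial is open-label with the ward doctor doing the rating.

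**Working it through.** **Inputs from the documents.** Allocation is 1:1 (Trial design). Under Sample size calculation: 80% power, two-sided 5%, "a sample size of 26 patients per arm is required to detect an effect size of 0.80", and "anticipated drop out of 10%, 58 patients will be included". These figures are for CSQ-8J. The article gives no power statement for BPRS.

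**The plan's own figure.** The normal approximation at 0.80 SD gives 25 per arm. The two-sample t test gives 25.5, so 26 per arm, with power 80.7%. For dropout, 52 / 0.90 = 57.8, so 58. The stated sample size reproduces, and 26 per arm is used below.

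**Assumption.** The correlation r between admission and discharge BPRS is not in the documents. A range from 0 to 0.7 is shown.

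**Chance imbalance at admission.** The standard error of the difference in mean admission BPRS, in SD units, is sqrt(2/26) = 0.277.
- P(|difference| > 0.3 SD) = P(|Z| > 0.3/0.277) = 28%.
- P(|difference| > 0.5 SD) = P(|Z| > 0.5/0.277) = 7%.

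An unadjusted comparison of discharge scores carries r times the imbalance. For a 0.3 SD imbalance the shift is 0.3 × r.

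**Precision.** Relative to an unadjusted comparison of discharge scores, the ANCOVA variance factor is (1 - r²) × (1 + 1/(N - 4)). The second term is the cost of the degree of freedom spent. With N = 52 it is 1 + 1/48 = 1.021. At r = 0.5, for example, 0.75 × 1.021 = 0.766. The equivalent n per arm is 26 divided by the factor. The smallest difference detectable with 80% power is 0.79 SD unadjusted, multiplied by the square root of the factor when adjusted. Power is shown for an illustrative true difference of 0.5 SD, where the unadjusted test has 42%.

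| r | Shift from a 0.3 SD imbalance | Variance factor | Change in variance | Equivalent n per arm | Detectable difference (SD) | Power at 0.5 SD |
|---|---|---|---|---|---|---|
| 0 | 0 | 1.021 | +2% | 25.5 | 0.80 | 42% |
| 0.2 | 0.06 SD | 0.980 | -2% | 26.5 | 0.78 | 43% |
| 0.3 | 0.09 SD | 0.929 | -7% | 28.0 | 0.76 | 45% |
| 0.5 | 0.15 SD | 0.766 | -23% | 34.0 | 0.69 | 52% |
| 0.7 | 0.21 SD | 0.521 | -48% | 49.9 | 0.57 | 69% |

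**If the change score is meant.** Assuming equal SDs at the two times, its variance relative to the discharge score is 2(1 - r): 2.0 at r = 0, 1.4 at 0.3, 1.0 at 0.5 and 0.6 at 0.7. ANCOVA has the smaller variance at each of these values. The change score does use the baseline, but it carries (r - 1) times the imbalance, which has the opposite sign: at r = 0.5, a 0.3 SD imbalance shifts it by -0.15 SD.

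**If all 58 are analysed (29 per arm).** The standard error of the imbalance is 0.26 SD and P(> 0.3 SD) is 25%. The picture is the same.

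**The case against.** A reader might infer that the plan refuses to adjust for admission BPRS. The article does not say that. The words introducing the covariates make the list illustrative, so admission BPRS could be added without contradicting the text. Nor can one say that the admission score goes unused, because the outcome may be the change score. Both objections stand. What the text supports is that the score is not named and the outcome variable is not settled.

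A reader might also infer that the unadjusted comparison is biased, or that an imbalance at admission passes through in full. Neither follows. Randomisation keeps the estimate unbiased on average and the test keeps its type I error. The imbalance matters only conditionally on the allocation obtained, and only r times it carries over.

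The gain cannot be claimed as large, or as free in every case. No correlation is given, and a low one is plausible: ratings at acute admission and at discharge are separated by treatment over an average stay of 45 days. At r of about 0.2 or less the gain is negligible, and at r = 0 about 2% is lost. The table also compares with no covariates at all. The gain over the planned model, which already has sex, age and duration of illness, has not been computed.

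Finally, a full covariate list is often left to a statistical analysis plan, and so is the choice of predictors for the multiple imputation, on which no defect is shown. The first part of this answers the point only partly. The article does set out the tests, the model family and example covariates for this outcome, and a better method is available from data already collected.

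**Conclusion.** The point holds as a modest improvement to a stated analysis, not as an error. The plan commits to no use of admission BPRS and leaves the symptom-severity variable undefined. If discharge scores are compared without it, the result is exposed to a chance imbalance that exceeds 0.3 SD in about 28% of such trials, and the resulting shift is 0.09 to 0.21 SD for r between 0.3 and 0.7.

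The effect of adjustment on variance runs from a 2% loss at r = 0 to a 48% reduction at r = 0.7, and it becomes material from about r = 0.5. All of this rests on an assumed r. The trade is favourable because the possible loss is small and the possible gain is not.

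It concerns a secondary outcome for which no power is claimed. The 26 per arm, the total of 58 and the CSQ-8J primary analysis are untouched.

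**What to change.** Add one sentence to Statistical methods: symptom severity is the BPRS score at discharge, and its main analysis is an ANCOVA with arm, admission BPRS, sex, age and duration of illness as terms. The unadjusted comparison can stay as a supporting result.

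The cost is that sentence and one degree of freedom. No new data are needed, since the admission rating is already routine. It should be confirmed that this rating is made before allocation. The article's sequence suggests so: candidates are nominated within three days of admission, and randomisation follows consent.
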